## Abstract

Spinal cord injury and traumatic brain injury are major causes of long-term disability and are often complicated by spasticity, a motor disorder characterized by increased muscle tone and exaggerated reflexes that significantly impair quality of life. Current diagnostic methods lack the sensitivity needed to accurately predict the severity of injury or the onset and progression of spasticity. Trauma-induced calcium dysregulation activates calpains, a family of proteases that cleave sodium channels, disrupting their inactivation and increasing persistent sodium currents. This cascade drives the overexcitability of motoneurons, contributing to the development of spasticity. Consequently, sodium channel fragments have emerged as promising biomarkers that link injury mechanisms to clinical outcomes. The present SpasT-SCI-T clinical trial protocol aims to evaluate sodium channel fragments as blood biomarkers for assessing the severity of spinal cord and traumatic brain injuries, as well as their potential to predict clinical outcomes, including the development of spasticity. This prospective, multicenter, case-control and cohort study involves 40 participants: 20 individuals with spinal cord injury, 10 individuals with traumatic brain injury, and 10 healthy controls. Blood samples are collected within six hours of injury and at follow-up points over six months. Clinical outcomes, including spasticity (assessed using the Modified Ashworth Scale), neurological recovery (measured by the American Spinal Injury Association Impairment Scale and Glasgow Coma Scale), and quality of life (evaluated using the Short Form-36 Health Survey), are analyzed in correlation with biomarker levels. We anticipate that calpain-mediated sodium channel fragments will transform the management of central nervous system injuries by enabling early diagnosis, improving prognostic accuracy, and guiding personalized therapeutic strategies. The clinical trial is registered on ClinicalTrials.gov (NCT06532760, January 10, 2024), with Assistance Publique–Hôpitaux de Marseille as the sponsor.

## Introduction

Spinal cord injury (SCI) is a tragic condition with lifelong physical, psychological, and economic consequences, affecting millions of individuals worldwide [1–3]. Accurate and timely assessment of its severity is paramount for predicting outcomes and guiding therapeutic interventions. However, current diagnostic methods, which rely primarily on clinical examinations and imaging, lack the sensitivity required for precise evaluation, especially during the critical acute phase [4–6]. This diagnostic gap underscores the urgent need for novel, reliable biomarkers to improve clinical decision-making.

One of the most prevalent and disabling complications of SCI is spasticity, which affects up to 75% of patients within the first year post-injury [7,8]. Spasticity, classically defined as hypertonia with a velocity-dependent increase in stretch reflexes [9], encompasses a spectrum of clinical manifestations, including clonus, exaggerated reflexes, muscle spasms, and involuntary leg crossing [10,11]. These symptoms severely disrupt daily activities, quality of life, and rehabilitation efforts. Without early and effective management, spasticity progresses to complications such as muscle shortening, joint contractures, and painful pressure sores [12,13]. The unpredictable onset and variable severity of spasticity, ranging from mild stiffness to severe, uncontrollable spasms, pose significant challenges for clinicians, emphasizing the urgent need for reliable predictive biomarkers [14,15].

Advances in our understanding of spasticity pathophysiology have highlighted promising targets for biomarker discovery [16,17]. Secondary injury processes in SCI trigger molecular cascades, including excessive glutamate release, intracellular calcium overload, and calpain activation [18,19]. Calpains, calcium-activated proteases, cleave Nav1.6 voltage-gated sodium channels [20–22], which are predominantly expressed in spinal motoneurons [23–25]. This proteolysis disrupts the normal inactivation of Nav1.6 channels, leading to an upregulation of persistent sodium currents (I_NaP_) [20–22]. The pathological I_NaP_ drives motoneuron hyperexcitability and sustained depolarizations (plateau potentials), directly contributing to spasticity in both animals [26–31] and humans [32–34].

The identification of sodium channel fragments as products of calpain-mediated cleavage offers a novel biomarker opportunity, linking the molecular pathology of SCI to clinical outcomes. These fragments hold potential not only for assessing SCI severity but also for predicting the onset and magnitude of spasticity [21]. Notably, similar sodium channel cleavage mechanisms have been observed in traumatic brain injury (TBI), suggesting broader applicability of these biomarkers across central nervous system (CNS) injuries [35–37].

The focus on SCI and TBI in this study is thus driven by their shared traumatic etiology and the established role of calpain-mediated sodium channel cleavage in their pathophysiology. SCI, with its high prevalence of spasticity (up to 75% of patients), and TBI, a leading cause of CNS trauma, both exhibit this molecular signature in preclinical models [21,35–37], distinguishing them from non-traumatic CNS conditions such as stroke or neurodegenerative diseases, where this mechanism is not documented. By targeting these traumatic injuries, we aim to leverage this specific biomarker to address the unmet diagnostic and prognostic needs in acute CNS trauma management.

The present *SpasT-SCI-T* clinical trial protocol aims to evaluate calpain-mediated sodium channel fragments as diagnostic biomarkers for SCI and TBI and as prognostic markers for spasticity. By bridging molecular mechanisms and clinical outcomes, this study seeks to advance the management of CNS injuries and spasticity, paving the way for more accurate diagnoses, enhanced prognostic precision, and personalized therapeutic strategies.

## Methods and analysis

### Study aims

The primary objective of the SpasT-SCI-T study is to detect and quantify sodium channel fragments in blood samples from patients with SCI or TBI. These fragments will be measured at multiple post-trauma time points, ranging from 6 hours to 6 months after injury.

The secondary objectives are threefold:

To characterize in SCI and TBI patients the temporal kinetics of sodium channel fragments, providing insight into their dynamic expression and persistence over time.To evaluate the relation between plasma fragment levels and the onset, progression, and severity of spasticity in SCI patients.To compare plasma fragment levels in SCI and TBI patients with those of healthy controls, establishing baseline values and identifying injury-specific signatures.

### Study design

The SpasT-SCI-T study is a prospective, multicenter observational trial performed in France. The study employs a combination of case-control and cohort designs to address its primary and secondary objectives. The inclusion of patients will officially begin on March 17, 2025 and end on September 20, 2026. A total of 40 participants are recruited, divided into three groups:

1**Group 1 (Healthy Controls):** Ten healthy volunteers provide baseline blood samples for comparison.2**Group 2 (SCI Patients):** Twenty patients with acute traumatic SCI confirmed by imaging and no associated TBI.3**Group 3 (TBI Patients):** Ten patients with acute TBI confirmed by imaging and no associated SCI.

The trial consists of three phases:

1**Inclusion Phase:** Participants are enrolled into one of the three study groups based on predefined eligibility criteria.2**Acute Phase (0–14 days):** This phase focuses on the immediate response to trauma, capturing rapid changes in sodium channel fragment levels during the critical early period. Blood samples are collected within 6 hours post-trauma and at multiple time points (Days 1, 3, 5, 7, and 14) to monitor early biomarker kinetics.3**Late Follow-Up Phase (3 and 6 months):** The late follow-up phase assesses long-term changes in sodium channel fragment levels and their association with recovery trajectories and clinical outcomes, including the onset and severity of spasticity. Blood samples are collected during follow-up consultations at 3 and 6 months post-trauma. A 6-month follow-up was selected as clinical signs of spasticity typically stabilize between 2 and 6 months post-injury, with electrophysiological measures showing minimal change thereafter [38].

The CONSORT diagram in Fig 1 provides details on the timeline for enrollment, interventions, and assessments across the participant groups, while the overall study design is summarized in Fig 2.

**Fig 1 pone.0319635.g001:**
[figure not shown]
CONSORT flow diagram of the SpasT-SCI-T study. (SCI: spinal cord injury; TBI: traumatic brain injury; MAS: modified Ashworth scale; ASIA: American Spinal Injury Association; GOS: Glasgow Outcome Scale; H: hour; D: Day; M: Month). Patients under proxy or emergency consent who regain capacity are re-consented, with the option to withdraw and request retrospective data withdrawal.

**Fig 2 pone.0319635.g002:**
[figure not shown]
Graphical overview of SpasT-SCI-T study design. Overview of the three study groups and their respective schedules for blood sample collections and clinical assessments. Group 1 (10 healthy subjects) provides a single baseline blood sample. Group 2 (20 SCI patients) and Group 3 (10 TBI patients) undergo sampling within 6 hours post-trauma, during the early follow-up phase (days 1, 3, 5, 7, and 14), and at late follow-ups (3 and 6 months). Clinical assessments include the American Spinal Injury Association (ASIA) impairment scale, Glasgow Coma Scale (GCS), Glasgow Outcome Scale (GOS), and Modified Ashworth Scale (MAS), depending on the group. These outcome measures are defined and detailed in the “Outcomes” section.

### Ethics approval and consent

The SpasT-SCI-T study was approved by the Comité de Protection des Personnes Est III (CPP Est III) on October 7, 2024 (CPP number 2024-A00265-42). Written informed consent was obtained from all participants or their legally authorized representatives prior to inclusion. For conscious patients, consent was secured directly using the model consent form within 6 hours post-trauma. For unconscious or incapacitated patients, proxy consent was obtained from a legally authorized representative, with continuation consent sought from the patient upon recovery of decision-making capacity. In emergency cases where no proxy was available within the 6-hour inclusion window, a physician not involved in the study authorized initial inclusion, followed by written consent from the patient or representative as soon as feasible, in compliance with Article L1122-1–3 of the French Public Health Code. Consent was not waived for any participants.

### Sites and ressources

The trial spans 30 months and is performed within the Assistance Publique–Hôpitaux de Marseille (AP-HM) network, leveraging multiple specialized facilities for recruitment, data collection, and biological sample processing:

1**Neurosurgery Department, Hôpital Nord:** Led by [name], the Neurosurgery Department serves as the primary site for recruiting SCI and TBI patients. It specializes in acute neurological trauma management and advanced imaging (CT and MRI) to confirm eligibility. Follow-up visits at 3 and 6 months, including Modified Ashworth Scale (MAS) evaluations for spasticity in SCI patients, are coordinated here.2**Intensive Care Unit, Hôpital Nord:** Headed by [name], the center manages sever trauma patients during the acute injury phase and ensures the inclusion of patients unable to provide immediate consent. Baseline blood samples are collected within 6 hours post-trauma, with additional samples taken during early follow-up on Days 1, 3, 5, 7 and 14.3**Clinical Investigation Center, Hôpital Nord:** Healthy controls are recruited and assessed at this Center. It provides a controlled environment for obtaining informed consent and baseline blood samples. Standardized protocols ensure consistency across participant groups.4**BioMINT Platform, INT UMR7289, Aix-Marseille University la Timone:** Biological sample processing is centralized at the BioMINT platform, part of the Institute of Neurosciences (INT UMR7289). Plasma samples are analyzed using semi-automated Western blot techniques with Pan-Nav antibodies, ensuring high-quality, standardized biomarker data. Samples are stored at -80°C until analysis and transported monthly from clinical sites.5**Rehabilitation Centers for Long-Term Follow-Up:** Patients transitioning to affiliated rehabilitation centers within the AP-HM network participate in long-term follow-up. These centers collaborate with the Neurosurgery Department to ensure the collection of clinical data, including MAS evaluations, at 3 and 6 months post-trauma.

### Participants

The selection of participants is based on strict inclusion and exclusion criteria (Table 1).

**Table 1 pone.0319635.t001:** Inclusion and exclusion criteria for study participants.

Criteria	Group 1: Healthy Controls	Group 2: SCI Patients	Group 3: TBI Patients
**Age (years)**	18–75	18–75	18–75
**Type of Trauma**	None	Acute spinal cord injury (C4–T12), confirmed by CT/MRI	Acute traumatic brain injury (Marshall Grade II or higher), confirmed by CT
**Neurological Assessment**	None	ASIA Impairment Scale (grades A to D)	Glasgow Coma Scale (GCS ≤ 13)
**Inclusion Timeline**	–	≤6 hours post-trauma	≤6 hours post-trauma
**Associated Conditions**	-See Exclusion Criteria	No concomitant TBI	No concomitant SCI
**Social Security Affiliation**	Required	Required	Required
**Exclusion Criteria**	- Minor, Pregnancy or breastfeeding. - Pre-existing neurological disorders (e.g., multiple sclerosis, Parkinson’s disease), cardiovascular or pulmonary diseases. - Psychiatric illnesses or neurodegenerative conditions- Severe trauma (e.g., multi-organ failure) - Inability to provide consent and absence of a legally authorized representative	-Same as Group 1	-Same as Group 1

SCI, spinal cord injury; GCS, glasgow coma scale; TBI, traumatic brain injury; ASIA, American Spinal Injury Association.

Inclusion Criteria:

Group 1 (Healthy Controls):

Adults (male or female) aged 18–75 years.No history of central or peripheral nervous system trauma.Absence of any chronic neurological, psychiatric, or systemic diseases.Ability to provide informed consent prior to inclusion.Affiliation with a social security system.

Group 2 (SCI Patients):

Adults (male or female) aged 18–75 yearsConfirmed acute SCI (C4-T12) based on imaging (CT and MRI).Neurological assessment using the American Spinal Injury Association Impairment Scale (ASIA): grades A to D.Inclusion must occur within 6 hours post-trauma.No concurrent TBI.Affiliation with a social security system.

Group 3 (TBI Patients):

Adults (male or female) aged 18–75 yearsConfirmed acute TBI based on CT imaging (Marshall Grade II or higher).Neurological assessment using the Glasgow Coma Scale (GCS) ≤13.Inclusion must occur within 6 hours post-trauma.No concurrent SCI.Affiliation with a social security system.

Exclusion Criteria (All Groups):

Pregnancy or breastfeeding.Pre-existing neurological disorders, such as multiple sclerosis or Parkinson’s disease.History of psychiatric illness or neurodegenerative conditions.Concurrent severe trauma affecting study participation (e.g., multi-organ failure).Inability to provide consent, and absence of a legally authorized representative.Pre-existing cardiovascular or pulmonary diseases.

Informed consent is obtained from all participants using the model consent form and related documents after verifying their eligibility according to the inclusion and exclusion criteria. Recognizing the urgency of inclusion and the acute medical care context, the consent process is tailored to accommodate the specific needs of SCI and TBI patients. The following procedures ensure compliance with ethical and legal requirements while prioritizing participant autonomy and rights:

1**For conscious patients** capable of decision-making, informed consent is obtained directly within the 6-hour inclusion window. The investigator or clinical team provides the patient with a detailed information sheet outlining the study’s objectives, procedures, potential risks and benefits. Patients are given the opportunity to ask questions and are encouraged to make an informed decision. Once all concerns are addressed, they sign the consent form, confirming their voluntary participation.2**For unconscious or incapacitated patients**, a legally authorized representative (e.g., a close relative) is approached to provide proxy consent. The representative is provided with the same detailed information about the study, and their consent is carefully documented. Once the patient regains the capacity to decide, they are fully informed about their participation, following the same process as for conscious patients. This involves a prompt visit from the investigator or a trained clinical team member, who provides a detailed information sheet and verbally explains the study’s objectives, procedures, risks, benefits, and their prior inclusion under emergency or proxy consent. Patients are given ample time to ask questions and consider their options. Written continuation consent is then requested to confirm their voluntary agreement to remain in the study. If they decline continuation consent, they may withdraw from the study and can request retrospective withdrawal of data collected prior to regaining capacity, in accordance with Article L1122-1–1 of the French Public Health Code and GDPR. Such data will be destroyed unless already anonymized and aggregated for analysis. These procedures comply with Article L1122-1–3 of the French Public Health Code, ensuring adherence to legal and ethical standards for proxy and emergency consent.3**Emergency Consent:** In cases where the patient is unconscious and no proxy is available within the inclusion timeframe (6 hours post-trauma), a physician not involved in the study may authorize emergency consent. This process allows for the patient’s inclusion while ensuring that: 1) Consent is obtained as soon as possible from the patient or their representative once circumstances allow. Once the patient regains capacity or a relative is available, they are fully informed of their inclusion and written consent is requested, in compliance with Article L1122-1–3 of the French Public Health Code. The re-consent and withdrawal process outlined above applies in these cases, ensuring patients retain full autonomy over their participation and data.4For **healthy volunteers**, written informed consent is obtained prior to any study-related procedures. The consent process ensures they understand the study’s objectives, any potential risks, and their right to withdraw at any time without consequences.

All participants, regardless of group, continue to receive standard medical care, including routine imaging, rehabilitation, and clinical follow-ups, without interference from study procedures. Withdrawal from the study, whether initiated by the participant or deemed necessary for medical reasons, does not impact their access to or quality of standard medical care.

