### Sphincter functions

Sphincter function is a crucial outcome in SCI patients, as SCI often compromise bladder and bowel control, significantly affecting quality of life. Assessments include bladder management (permanent or intermittent catheterization, normal urination) and bowel function (fecal incontinence, constipation), focusing on their impact on quality of life.

The **Table 3** summarizes the main data collected from the patients in the case report forms, from their inclusion in the study to the 6-month follow-up consultation.

**Table 3 pone.0319635.t003:** Main data collected from the patients in the case report forms, from their inclusion in the study to the 6-month follow-up consultation (ASIA: American Spinal Injury Association; GCS: Glasgow Coma Scale; BASIC: Brain and Spinal Injury Center [41]; AOSpine [39]; AIS: Abbreviated Injury Score; ISS: Injury Severity Score [48]; SAPS II: Simplified Acute Physiology Score II [49]; SOFA: Sepsis related Organ Faillure Assessment [50]; Kdigo [51]; modified Ashworth scale [44]; DN4 [47]; GOS: Glasgow Outcome Scale; GOSE: Glasgow Outcome Scale Extended [45]; SF36: Short Form 36 Health Survey [46]).

Inclusion	Hospital discharge	3 and 6-month follow-up
Background: -Gender -Age -Height -Weight Medical history: -Organ failure: heart, lung, kidney -Diabetes and chronic diseases -Cancer -Addiction: smoking, alcoholism	Spinal surgery: -Spinal stabilization -Spinal cord decompression -Levels Cranial surgery: -Intracranial lesion evacuation (craniotomy or craniectomy) -External ventricular drainage -Intracranial pressure monitoring Other surgery	Motricity: -Bed rest -Wheelchair use -Walking with assistance -Slow walking without assistance -Walking normally
Usual treatment: -Antiepileptic -Anticoagulant -Antihypertensive -Antidiabetic…	Additional treatments: -Analgesics -Antispasmodics -Antiepileptics -Antibiotics...	Additional treatments: -Analgesics -Antispasmodics -Antiepileptics -Antibiotics...
Trauma: -Date and time -Inclusion time -Type of accident	Intensive care stay: -Duration: stay, mechanical ventilation, sedation, intracranial pressure monitoring -Complications: refractory intracranial hypertension, infections (with treatment > 72 hours), septic shock, acute respiratory distress syndrome, acute renal failure (Kdigo > 3), cardiorespiratory arrest	Rehabilitation stay: -Medical complication -Specific support

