### Justification of sample size

The study includes a total of 40 participants distributed as follows: 20 patients with spinal cord injury (SCI), 10 patients with traumatic brain injury (TBI), and 10 healthy controls. The selection of 20 SCI patients is based on the annual admission rates for SCI at the study institution, ensuring a representative sample of the population served. The inclusion of 10 TBI patients is justified to account for potential confounding factors arising from the overlapping but distinct injury mechanisms of SCI and TBI. Furthermore, 10 healthy controls are included to provide a robust baseline for sodium channel fragment levels, facilitating a balanced comparison across the three groups.

This sample size is sufficient to detect meaningful trends and associations between sodium channel fragments and clinical outcomes, including spasticity, while maintaining feasibility within the scope of a pilot study. The findings will generate preliminary evidence regarding the diagnostic and prognostic utility of sodium channel fragments in neurological injuries and will guide the design of larger-scale clinical trials.

Given the exploratory nature of this study, no formal interim analyses are planned. As the trial involves minimal-risk procedures, such as blood sampling, no pre-specified stopping rules have been established. In the event of significant deviations from the protocol or unforeseen safety concerns, the trial steering committee will consult the Ethics Committee to determine whether adjustments or study termination are necessary. All such decisions will be transparently documented and communicated to relevant stakeholders, including regulatory authorities, to ensure compliance with ethical standards.

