#### Baseline data.

Baseline data were systematically collected to characterize the study population and ensure comparability across the three participant groups (healthy controls, SCI patients, and TBI patients). Key baseline variables are presented in a detailed summary table to promote transparency and support balanced comparisons between groups.

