### Strengths and limitations

This study uniquely explores sodium channel fragments, providing an innovative and specific biomarker linked directly to calpain-mediated pathophysiology common to SCI and TBI. Unlike previous biomarkers, sodium channel fragments offer neuronal specificity, sustained temporal expression suitable for both acute and chronic phases, and potential for wide applicability in traumatic CNS conditions. Despite their promise, challenges remain before clinical adoption. Patient factors like demographics and comorbidities may affect fragment levels, requiring larger studies to define normative ranges and thresholds. Standardized sample processing is also essential for reproducibility. Integrating biomarker analysis into clinical workflows demands infrastructure and validation efforts.

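### Only controls must be free of chronic systemic disease, and the planned group comparison is unadjusted; add a comparison restricted to patients who meet the same rule

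*Protocol article*

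**What the plan says.** The inclusion list for Group 1 in the Participants section requires "Absence of any chronic neurological, psychiatric, or systemic diseases". The lists for Groups 2 and 3 have no counterpart. The exclusions for all groups cover pre-existing neurological disorders, "History of psychiatric illness or neurodegenerative conditions" and "Pre-existing cardiovascular or pulmonary diseases", besides pregnancy or breastfeeding, severe concurrent trauma and lack of consent. Diabetes, kidney disease and cancer are not among them.

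Table 1 does not show the control-only rule. Its exclusion row lists the common exclusions under Group 1 and marks both patient groups "Same as Group 1".

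Table 3, in its inclusion column, records "Organ failure: heart, lung, kidney -Diabetes and chronic diseases -Cancer" as medical history.

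Under Statistical methods, the three groups are compared by one-way ANOVA or Kruskal-Wallis with pairwise tests to follow, and no covariates. A multivariable regression is described afterwards. Comorbidities may enter it if they are statistically significant or clinically relevant, and its stated purpose is to protect associations with outcomes such as spasticity.

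Baseline data says that baseline variables were collected to "ensure comparability across the three participant groups (healthy controls, SCI patients, and TBI patients"). Strengths and limitations concedes that "Patient factors like demographics and comorbidities may affect fragment levels".

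**The concern.** Eligibility itself makes the groups unequal on a factor that the article says may move the biomarker. Chronic systemic disease can occur among the patients and cannot occur among the controls, so the imbalance goes one way. It would remain even if the groups were matched on age and sex.

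Study aims uses the comparison with controls to set reference values and to find patterns specific to injury, and Statistical methods treats it as part of the primary objective. If chronic disease shifts fragment levels, part of an observed difference belongs to prior health and not to the injury. The reference values would also come from people healthier than the patients were before their trauma. Collecting baseline data documents this imbalance but does not remove it.

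**Working it through.** **Inputs.** Group sizes come from Justification of sample size: "20 patients with spinal cord injury (SCI), 10 patients with traumatic brain injury (TBI), and 10 healthy controls". The two-sided 0.05 level comes from Statistical methods. The article gives no SD, effect size, power or comorbidity rate, so there is no stated figure to reproduce. Two quantities are assumed: the share *p* of patients with a permitted chronic disease (10-50%) and the shift *g* that it causes in fragment level (0.5-1.0 SD).

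**Step 1: bias of the unadjusted contrast.** With injury effect *d*, the expected patient mean minus the expected control mean is *d* + *p* × *g*, because *p* = 0 in controls by rule. The bias is therefore *p* × *g*:

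| Share | g = 0.5 SD | g = 1.0 SD |
|---|---|---|
| 10% | 0.05 | 0.10 |
| 20% | 0.10 | 0.20 |
| 30% | 0.15 | 0.30 |
| 50% | 0.25 | 0.50 |

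A simulation (4,000 runs per cell, 30 patients v 10 controls, *d* = 1 SD) gave 0.051 to 0.499 SD across the same range.

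**Step 2: can it be removed?** Take a model with an intercept, SCI, TBI and a disease indicator that is zero in all 10 controls. With 1, 3, 6 or 9 of the 30 patients diseased, the design matrix has rank 4 of 4, so group and disease effects are separately estimable. Rank drops to 3 only if no patient or every patient is diseased. In the simulation, the contrast adjusted for disease and the contrast restricted to disease-free patients both had bias of at most 0.01 SD.

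The adjusted coefficient can be read as the injury effect for all patients only if disease shifts fragment levels equally with and without injury. No control has disease, so the data cannot test that. The restricted contrast does not need the assumption, but it speaks only for people without chronic disease.

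**Step 3: price of restriction.** The standard error is √(1/10 + 1/*n*) in SD units:

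| Patients kept | SE | Power at d = 1 SD |
|---|---|---|
| 30 (all) | 0.365 | 78% |
| 27 (10% comorbid) | 0.370 | 77% |
| 21 (30%) | 0.384 | 74% |
| 15 (50%) | 0.408 | 69% |

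For SCI alone, 20 v 10 has SE 0.387. It becomes 0.414 with 14 v 10 and 0.447 with 10 v 10.

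**Step 4: false positives.** With no injury effect and *g* = 1 SD, a Mann-Whitney test of 20 v 10 on its own rejects 6.3%, 9.2% and 12.9% of the time at 20%, 30% and 40% comorbid, against about 4.5% with none. The plan uses pairwise tests as a follow-up to the omnibus test. If both must reject, with SCI and TBI patients equally affected, the rates are about 3%, 5% and 7-8%, against 2.3% with none (20,000 runs). At 1.5 SD and 40% the rate is about 13%, against about 21% for Mann-Whitney alone.

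**The case against.** Five points weigh on the other side.

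- **The bias is not beyond repair.** A reader might infer that chronic disease is so tied to patient status that no model can separate the two. Step 2 shows otherwise: disease varies among patients, so both adjustment and restriction work. What cannot be estimated is the patient-control contrast among people with chronic disease.
- **Comorbidity is already in the plan.** The regression can include diabetes, organ failure and renal clearance. This stands only in part. Its stated target is associations with outcomes such as spasticity. Injury severity, one of its main factors, has no value in controls. Comorbidities enter conditionally, and selecting them by significance with 40 participants can drop a real confounder. A sensitivity analysis might also sit in an analysis plan that is not shown, but the comparison that the article does fix is unadjusted.
- **Table 1 is not false.** A reader might infer that it declares the full criteria identical. The cell stands in the exclusion row and describes the common exclusion list correctly. The fault is that the table omits the control-only inclusion rule.
- **Table 3 is a checklist.** It lists heart and lung failure although cardiovascular and pulmonary disease are excluded throughout, so it says nothing about how common these diseases will be.
- **Healthy volunteers are an ordinary reference group in a pilot study.** That is fair. The point does not ask for different controls, only for an estimate that compares like with like.

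**Conclusion.** The concern holds in a limited form. Eligibility differs by group on chronic systemic disease, the article concedes that comorbidity may affect the biomarker, and the planned group comparison makes no allowance for it. The resulting bias is about share times effect: 0.3 SD at 30% and 1 SD, and 0.05 to 0.50 SD over the assumed range. At 10% comorbid or a 0.5 SD shift it is small.

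Both inputs are assumptions, so the size is uncertain while the eligibility difference is not. The documents do not support a claim of complete confounding, nor of large false-positive inflation under the planned test sequence except at the upper end of those assumptions. The point is a cheap improvement to the analysis and wording, not a flaw that invalidates the design.

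**What to change.** 1. Alongside the three-group comparison in Statistical methods, pre-specify the patient-control estimate with its confidence interval, restricted to SCI and TBI patients who meet the Group 1 chronic-disease criterion as judged from the Table 3 medical history. Report it with the primary estimate whenever a difference is attributed to injury. A model with group and disease terms may be added, with its equal-effect assumption stated.
2. Add the control-only rule to Table 1.
3. Under Baseline data, replace the claim that data collection secures comparability with a statement that the groups differ by design on chronic disease.

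The cost is one further analysis of data already collected and two changes of wording. Recruitment and procedures stay as they are. The drawback is fewer patients and the modest loss of precision shown in Step 3, and the restricted result applies to people without chronic disease.
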